### Nested substudies

A PK substudy is currently underway in selected African and Asian sites and will provide important data on drug exposure of all trial TB drugs (sourced from the same manufacturer) and their relationship with toxicity (eg, drug-induced liver injury (DILI)) and response. Pharmacogenetic substudies (eg, acetylator status) to evaluate genetic differences affecting exposure to TB drugs are planned. In-depth characterisation of longitudinal neuroimaging with MRI will assess the impact of aspirin on cerebral ischaemia/infarcts, as well as neurocognitive and epilepsy outcomes. Substudies on pathophysiology, epilepsy and health economic evaluations are also underway (table 3). SURE also has a multi-site nested substudy for the discovery of novel diagnostic and prognostic biomarkers in CSF and non-CSF clinical samples. Using a case-control design, controls for the diagnostic substudy are children who fail screening and have an alternative diagnosis. Embedding this design into the trial framework allows full use of all screened participants and sensitises parents/carers to lumbar punctures, which is beneficial in settings where lumbar puncture refusal is high. Diagnostic challenges are also opportunities for capacity strengthening (eg, lumbar puncture workshops and educational videos on consenting carers/parents to lumbar puncture).

### Serious AEs (SAEs) and safety reporting

The definitions in the European Union (EU) Directive 2001/20/EC, Article 2, based on the principles of Good Clinical Practice (GCP), apply to this trial protocol. Serious adverse reactions (ARs) include any untoward or unintended response to drugs.

All SAEs meeting the definitions as per the EU guidance (ENTR/CT 3, April 2006 revision) are reported regardless of their relationship to TBM. AEs and/or ARs (serious and non-serious) are graded using the toxicity gradings in the 2017 Division of AIDS (DAIDS) toxicity grading V.2.1.

An AE is deemed to be serious if it meets one of the pre-defined six criteria online supplemental
table S5, row 4. The investigator provides a causality assessment of all serious events in relation to the trial therapy.

Where causality is assessed as unrelated or unlikely to be related to trial medication, the event is classified as an SAE. Where causality for SAE is assessed as possible, probable or definitely related to trial medication, the event is classified as a serious AR (SAR). SARs will also undergo an expectedness assessment by the MRCCTU Clinical Reviewer, and if deemed unexpected, the SAR is classified as a suspected unexpected SAR and requires expedited regulatory reporting.

All SAEs occurring from the time of randomisation until the participant’s final 72-week follow-up visit are reported. SARs are notified until trial closure.

### Events of interest

A number of events that could have an impact on drug management but would not be considered serious and therefore not constitute an SAE are reported as an Event of Interest (EOI) as in Box 2.

Box 2Event of interestGrade 3/4 adverse event/reaction.Gastrointestinal bleeding (any grade).Drug-induced liver injury (grade 2 and above).New development of obstructive hydrocephalus.Suspected relapsed tuberculosis disease.Tendonitis or tendon pain (any grade).Muscle/joint aching/pain (grade 2 or above).

Pregnancy is reported as an EOI in an expedited manner. Pregnancy-related events do not constitute SAEs unless they result in a condition that meets the seriousness criteria defining SAEs (eg, septic abortion). All pregnancies are followed up until their outcome is known and recorded.

### Withdrawal of trial treatment

Protocol treatment discontinuation is considered under any of the following circumstances:

Unacceptable toxicity or AE.Intercurrent illness that prevents further treatment.Any change in the patient’s condition that justifies the discontinuation of treatment in the clinician’s opinion.Withdrawal of consent for treatment by the patient or parents/carers of young children.Suspected treatment failure.Drug resistance (ATT-specific).

Children who have protocol treatment discontinued remain in the trial for the purpose of follow-up and data analysis (including up until the time a carer withdraws consent for follow-up if this occurs). Data are kept and included for patients who stop follow-up early, up to the point of exit.

### Patient and public involvement

Patients and public representatives who are survivors of TBM (from Vietnam and Zimbabwe) will be involved in the dissemination of study results to participants and linked communities. There was no specific patient and public engagement at the time of study design, protocol development or recruitment and retention, in part because of the global COVID-19 pandemic.

### Data handling and data management

Each site is responsible for its own data entry and local trial management. Data are entered into the trial database directly at the site and checked centrally by authorised personnel. Data are checked for missing or unusual values and consistency within participants over time. When problems are identified, sites are contacted to verify or correct data entries on the original case report form (CRF) and the database.

### Quality control (QC) and assurance

The quality assurance and QC considerations have been based on a formal risk assessment. This risk assessment has been reviewed by the MRCCTU’s research governance committee and has led to the development of a data management plan, safety reporting plan and monitoring plan, which are separately reviewed by the MRCCTU Quality Management Advisory Group.

### Monitoring

Staff from the relevant clinical trial unit (CTU) visit clinical sites to validate and monitor data, and when this is not practical, an independent local monitor makes regular monitoring visits to the trial sites. The frequency, type and intensity of routine on-site monitoring and the requirements for triggered monitoring are detailed in a monitoring plan. Central monitoring occurs at MRCCTU through regular database reviews and reviews by the trial statistician for missing or inconsistent data. Queries are raised to sites that are responsible for their resolution.

### Statistical considerations

#### Sample size

The study is powered by the comparison of the shortened ATT versus standard control ATT, as this requires a larger number of patients. Based on a non-inferiority margin of 10%, 394 (rounded to 400) children would be needed to demonstrate non-inferiority, with 90% power, 2-sided 5% alpha and 5% loss to follow-up at 1 year, assuming 20% mortality in the control regimen and 17% (ie, a 3% (absolute) improvement) in the intensified shorter regimen. Control arm estimates are based on a recent meta-analysis,^3^ and the assumption of a 3% improvement in the intervention arm is based on the reported lower mortality with the intensified short regimen used in Cape Town.^15^

Assuming 50% of children in the placebo arm die or suffer severe impairment,^3^ 400 children would provide approximately 90% power, 2-sided 5% alpha, to detect a difference of at least 16% (superiority margin) in the aspirin arm when compared with placebo. The largest TBM aspirin trial to date reported 45% and 50% reductions in stroke and mortality, respectively.^41^ Following regular consultations with the independent data monitoring committee (IDMC) and trial steering committee (TSC), if the planned recruitment of 400 children is not possible, the modified target of 300 children would be acceptable to allow 80% power and 350 children to allow 85% power.

#### Statistical analysis plan (SAP)

Analysis populations for both randomisations will be (1) intention to treat (ITT) population defined as all randomised children who took at least 1 dose of the trial drug (either ATT or aspirin), (2) modified ITT (mITT) defined as ITT excluding late screening failures (ie, those randomised but subsequently not found to have TBM) and (3) per-protocol population defined as mITT excluding those not taking at least 80% of allocated treatment (unless in case of death). The latter also includes enrolled participants who were later found to be ineligible due to a major protocol deviation affecting efficacy (eg, rifampicin resistance).

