Box 1Inclusion and exclusion criteriaInclusion criteriaAged between 29 days and less than 18 years.Weight ≥3 kg.Symptoms compatible with TBM.CSF results are compatible with TBM, with or without AFB on microscopy or *Mycobacterium tuberculosis* on GeneXpert (or other validated NAATs), *or* the physician believes the child needs immediate initiation of anti-TB drugs.Known (or pending confirmation of) HIV status.The parent/legal guardian gives informed, written consent.Agree for a CSF sample to be collected and processed for chemistry, microscopy, Ziehl-Neelsen or auramine stain and mycobacterial culture (in process), and, where available, Xpert or Xpert Ultra prior to commencing treatment or when clinically stable to do so. Where patients have already been started on ATT, prescreening CSF should be available.The participant’s carer/parent can comply with the protocol requirements in the opinion of the site investigator.Exclusion criteriaRecent contact (last 12 months) with known or suspected rifampicin-resistant TB.Proven drug resistance to rifampicin in the child.On ATT for >21 days.Severely moribund; high risk of death within 24 hours based on clinical judgement.History or presence of known allergy or other contraindication to any first-line anti-TB drugs, corticosteroids or aspirin.Pregnancy.History of gastrointestinal bleeding or bleeding diathesis.Active clinical infection with influenza or varicella.Grade 4 liver toxicity (ALT and/or AST ≥10× upper limit of normal) or other contraindications* for taking part in the trial.AFB, acid fast bacilli; ALT, alanine transaminase; AST, aspartate aminotransferase; ATT, antituberculosis therapy; CSF, cerebrospinal fluid; HIV, human immunodeficiency virus; NAAT, nucleic acid amplification test; TB, tuberculosis; TBM, tuberculous meningitis. *Other contraindications are rare and allow the attending physician to make a decision at their own discretion about whether a participant is eligible. For example, a history of long QT syndrome, being already on several high-risk drugs and concern for an increased risk if randomised to short ATT, which includes levofloxacin.

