#### Primary analysis

Primary outcomes for *randomisation 1* is mortality from all causes at 48 weeks. The primary analysis is based on the difference in proportion of deaths between the two arms at 48 weeks. The difference will be adjusted for minimisation factors using Cochran-Mantel-Haenszel weights. Alternative methods will be considered should sparse data within strata lead to unstable estimation.

Non-inferiority will be assessed using the upper bound of the two-sided 95% CI for this absolute difference. If the upper bound of this CI is less than 10% (the margin of non-inferiority), the intervention arm is considered to be non-inferior to the control arm.

*Randomisation 2* is designed to test for superiority of the aspirin versus placebo. mRS outcomes will be dichotomised as death (score 6) or severe impairment (score 5) versus the rest (score 0–4) and will be analysed using logistic regression adjusting for the minimisation factors.

As a secondary analysis, mRS will also be analysed using four groups: death or severe impairment (scores 5–6), moderate disability (scores 3–4), mild disability (scores 1–2) and full recovery (score 0).

This factorial trial assumes no statistical interaction between the two randomisations. An mITT analysis will be considered primary, and any exclusion from a full ITT analysis is detailed and justified in the SAP.

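### As worded, the per-protocol population keeps children found ineligible for efficacy-affecting reasons such as rifampicin resistance; probably a drafting slip, but the sentence needs correcting

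*Protocol article*

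**What the plan says.** The section headed Statistical analysis plan (SAP) defines three nested populations for both randomisations. ITT is all randomised children who took at least one dose. The mITT population is "ITT excluding late screening failures (ie, those randomised but subsequently not found to have TBM"). The third is the "per-protocol population defined as mITT excluding those not taking at least 80% of allocated treatment (unless in case of death"). The next sentence reads: "The latter also includes enrolled participants who were later found to be ineligible due to a major protocol deviation affecting efficacy (eg, rifampicin resistance").

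Three other places bear on this:

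- Box 1 (Setting and population) lists as an exclusion criterion: "Proven drug resistance to rifampicin in the child".
- Withdrawal of trial treatment lists, among the circumstances in which stopping protocol treatment is considered: "Drug resistance (ATT-specific").
- Primary analysis states: "An mITT analysis will be considered primary, and any exclusion from a full ITT analysis is detailed and justified in the SAP". For randomisation 1 the decision rule is: "If the upper bound of this CI is less than 10% (the margin of non-inferiority), the intervention arm is considered to be non-inferior".

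**The concern.** In a numbered list that ends with the per-protocol population, *the latter* is the per-protocol population, and the verb is *includes*. Children who failed an eligibility criterion, for a reason the article itself says affects efficacy, are therefore placed in the set meant to hold eligible, adherent children.

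This matters because randomisation 1 is a non-inferiority comparison. Children whose outcome does not differ between regimens pull the observed difference towards zero, which favours the non-inferiority conclusion. A per-protocol analysis is the usual check on that dilution, and a set that retains such children is a weaker check.

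The situation can arise in practice. Children are randomised as soon as eligibility and consent are confirmed (Randomisation and treatment allocation), whereas phenotypic susceptibility testing is done on positive cultures (Screening procedures). Resistance present at enrolment may therefore become known only afterwards.

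**Working it through.** **1. The wording, case by case.** Take a child with TBM whose rifampicin resistance, present at enrolment, is found after randomisation. The mITT exclusion does not remove the child, because it is glossed only as children found not to have TBM. Per-protocol membership is then as follows.

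| Child with resistance found later | 80% rule alone | Adding the next sentence as written | If that sentence meant exclusion |
|---|---|---|---|
| Protocol treatment stopped, under 80% taken, alive | out | in | out |
| At least 80% taken | in | in | out |
| Died | in (death exception) | in | out |

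In the first row the definition removes the child and then puts the child back. In every row the two readings of the disputed sentence give opposite answers. The third row shows that deleting the sentence would not be enough: a resistant child who died would stay in the set, and death is the primary endpoint of randomisation 1.

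**2. The plan's own sample size, to show that it is not in dispute.** The Sample size section states: "Based on a non-inferiority margin of 10%, 394 (rounded to 400) children would be needed to demonstrate non-inferiority". Its inputs are 20% mortality in control, 17% in intervention, a margin of 10 points, 90% power, two-sided 5% alpha and 5% loss.

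- Variance sum: 0.20 × 0.80 + 0.17 × 0.83 = 0.16 + 0.1411 = 0.3011.
- Distance to the margin: 0.10 + 0.03 = 0.13.
- Per arm: 0.3011 × (1.960 + 1.282)² / 0.13² = 187.2.
- Total: 374.4; divided by 0.95 = 394.1, which reproduces 394.

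Nothing in this depends on the per-protocol definition.

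**3. Size of the dilution, on assumed values.** The article gives no rate of rifampicin resistance, so the share f is an assumption and is shown as a range. In general, the difference in the whole set is (1 − f) × (difference in eligible children) + f × (difference in ineligible children). Assume the second difference is zero and that the truth in eligible children sits at the margin, 20% versus 30%. The expected difference is then 10 × (1 − f):

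- f = 2%: 9.8 points
- f = 5%: 9.5 points
- f = 10%: 9.0 points

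For scale, these shares of all 369 recruited children (Study status) would be about 7, 18 and 37 children.

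**4. Chance of wrongly meeting the 10-point criterion in that set.** With a normal approximation and unpooled variance, the chance is Φ((0.10 − d)/SE − 1.96), where d is the diluted difference. Worked case: 400 children less 5% loss leaves 190 per arm. With f = 5% and 20% mortality among the ineligible children in both arms, the rates are 20% and 29.5%.

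- SE = √[(0.16 + 0.208)/190] = 0.0440.
- Φ(0.005/0.0440 − 1.96) = Φ(−1.846) = 3.2%.

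Over 369 or 400 children less 5% loss, with mortality of 20%, 40% or 60% among the ineligible children, the results are:

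| f | One-sided chance of wrongly meeting the criterion |
|---|---|
| 0% (children excluded) | 2.5% |
| 2% | 2.8% |
| 5% | 3.2% |
| 10% | 4.0% to 4.2% |

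A real per-protocol set would be smaller than assumed here. Its standard error would be larger and the rise above 2.5% somewhat less.

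**The case against.** The strongest reply is that this is a slip of the pen. The clause before it is an exclusion, *also* reads as continuing a list of exclusions, and ineligibility for an efficacy-affecting deviation is ordinary grounds for leaving a per-protocol set. On that view *the latter* was meant to point to the excluded group, and the clash with the 80% rule is evidence of the slip and not a second defect. This is probably right about intent. It does not rescue the text, because no other sentence in the article says which reading holds.

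A second reply is that the article condenses a fuller plan and refers exclusions from ITT to the SAP. That stands to this extent: the SAP is not shown, and its definition may well be correct. The point is therefore about a rule the article states, not about one it omits.

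Three stronger readings are tempting, and the documents do not support them.

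- *The primary conclusion is biased by this sentence.* It is not. The mITT analysis is primary and no stated decision rule uses the per-protocol set. That set also still applies the adherence rule and, through mITT, the removal of children without TBM.
- *Resistant children must fare alike in both arms.* The article does not show this. The intervention also differs in levofloxacin and isoniazid dose, so a zero difference among them is an assumption, and the direction of the effect depends on it.
- *Confirmed cases are hit hardest, so the definite-TBM subgroup is most distorted.* Box 3 pools definite with probable TBM, and the subgroup analyses use mITT, so the per-protocol wording does not reach them.

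The number of affected children may also be small. Box 1 already excludes proven rifampicin resistance and recent contact with known or suspected resistant TB. Microbiological proof of TBM is not required, so later resistance could be shown in only some children.

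**Conclusion.** The sentence is wrong as written and should be corrected. Followed literally, it yields a per-protocol set that contradicts the set's purpose, sits against the eligibility criteria and reverses part of the preceding sentence. A drafting slip is the likeliest explanation, and the article should not be read as evidence of a deliberate choice to retain these children.

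The consequence is limited to the supportive per-protocol analysis of the non-inferiority comparison; sample size, power and the primary decision rule do not change. Within that analysis the lean towards non-inferiority is modest: up to 1 point off a true 10-point excess, and a one-sided error of at most about 4.2% against 2.5%, for shares up to 10%. These figures rest on two assumptions the documents do not supply: the share of such children, and equal mortality between arms among them.

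**What to change.** Replace the sentence with one that names the population and states the direction, for example: *Children later found to have been ineligible at enrolment for a reason that bears on efficacy, such as rifampicin resistance already present then, are also excluded from the per-protocol population.* Naming the population removes the ambiguous pronoun. Tying resistance to enrolment keeps the exclusion a matter of eligibility, so that resistance acquired on treatment, which is a secondary outcome in Table 2, does not remove a child.

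Then check that the SAP definition agrees, and settle it before any analysis by arm, since randomisation 1 is open-label. The cost is one sentence and a slightly smaller per-protocol set. No sample size, primary analysis or trial procedure changes.

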#### Primary analysis

Primary outcomes for *randomisation 1* is mortality from all causes at 48 weeks. The primary analysis is based on the difference in proportion of deaths between the two arms at 48 weeks. The difference will be adjusted for minimisation factors using Cochran-Mantel-Haenszel weights. Alternative methods will be considered should sparse data within strata lead to unstable estimation.

Non-inferiority will be assessed using the upper bound of the two-sided 95% CI for this absolute difference. If the upper bound of this CI is less than 10% (the margin of non-inferiority), the intervention arm is considered to be non-inferior to the control arm.

*Randomisation 2* is designed to test for superiority of the aspirin versus placebo. mRS outcomes will be dichotomised as death (score 6) or severe impairment (score 5) versus the rest (score 0–4) and will be analysed using logistic regression adjusting for the minimisation factors.

As a secondary analysis, mRS will also be analysed using four groups: death or severe impairment (scores 5–6), moderate disability (scores 3–4), mild disability (scores 1–2) and full recovery (score 0).

This factorial trial assumes no statistical interaction between the two randomisations. An mITT analysis will be considered primary, and any exclusion from a full ITT analysis is detailed and justified in the SAP.

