### Randomisation and treatment allocation

Randomisations occur immediately once eligibility criteria are confirmed and informed consent is obtained. Participants are randomised twice simultaneously (figure 1, *factorial design*) using a web-based, electronic randomisation system controlled through an authorised username and password to:

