**Figure 1 F1:**
[figure not shown]
Trial entry, randomisation and treatment. HD, high-dose; E, ethambutol; H, isoniazid; L, levofloxacin; R, rifampicin; TB, tuberculosis and Z, pyrazinamide. ˆ Target of 400. If planned recruitment to 400 is not possible, the modified target of 300 would be acceptable to allow 80% power and 350 to allow 85% power. * reduced mg/kg dosing used for children 25 kg and over. Both randomisations use minimisation with a random element and 1:1 allocation ratio.

6-month (24 weeks) intensive ATT regimen or a standard 12-month (48 weeks) ATT regimen in a 1:1 ratio (open-label).8 weeks of aspirin or matching placebo, in a 1:1 ratio (double-blinded).

Randomisation is a dynamic and concealed process; no preprepared lists are generated. Randomisation allocations are held securely within the Medical Research Council Clinical Trial Unit (MRCCTU) randomisation system and the Drug Supply Management System (DSMS). To randomise a participant, information is entered into an online trial database, and eligibility is automatically checked. On successful randomisation, the clinician prescribes allocated trial drugs. In all cases, neither the participant nor the investigator is notified of the treatment allocation of aspirin or placebo.

Aspirin and placebo are packed and prelabelled according to Good Manufacturing Practice guidelines with a code to maintain blinding for both trial site staff and participants recruited.

Since blinding of aspirin allocation is critical to the integrity of the study, all children are managed with the assumption that they receive aspirin. Unblinding during the trial is strongly discouraged unless it is a medical emergency and would alter clinical management. An emergency unblinding system for blinded randomisation can only be performed by a site principal investigator (PI) or allocated co-investigator through the DSMS. One unblinded delegated statistician has regular access to the treatment allocations for routine data querying and safety reporting purposes.

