#### Planned subgroup analysis

All subgroup analyses described here are exploratory. Subgroup analyses will be carried out and analysed for the primary efficacy endpoint for the mITT population. Subgroup analyses defined below will be performed for the mITT primary analysis for each randomisation 1 and 2 (Box 3).

Box 3Planned Subgroup analysesRegion* (Africa, India and Vietnam).Age group* (<2 years and ≥2 years).Sex (male and female).TBM stage using BMRC (1 and 2 combined, 3)*.ATT treatment prior to randomisation (< 7 days; ≥ 7 days)HIV status*.TBM baseline categorisation (definite and probable combined, possible).*Denotes minimisation factor. ATT, antituberculosis therapy; BMRC, British Medical Research Council and TBM, tuberculous meningitis.

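### Neither primary analysis names the other randomised treatment as a covariate: valid as written, but a small, removable amount of chance variation stays in each estimate

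*Protocol article*

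**What the plan says.** The Primary analysis section gives the adjustment set for both comparisons. For the 48-week mortality difference between ATT regimens: "The difference will be adjusted for minimisation factors using Cochran-Mantel-Haenszel weights", with the reservation "Alternative methods will be considered should sparse data within strata lead to unstable estimation". For the dichotomised mRS under aspirin or placebo, the outcome "will be analysed using logistic regression adjusting for the minimisation factors".

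Box 3, under Planned subgroup analysis, marks the minimisation factors with an asterisk ("Denotes minimisation factor"): region, age group, TBM stage and HIV status. The other allocation is not among them.

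Three further statements bear on the point:
- Under Randomisation and treatment allocation: "Participants are randomised twice simultaneously".
- In the caption to Figure 1: "Both randomisations use minimisation with a random element and 1:1 allocation ratio". The text does not say whether one allocation is balanced over the other.
- In Primary analysis: "This factorial trial assumes no statistical interaction between the two randomisations".

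**The concern.** In a factorial trial the second allocation is a baseline variable, recorded for every child and fixed by design. Assuming no interaction justifies analysing each margin over the other, but it does not imply that the other treatment has no main effect. If aspirin changes mortality and the two ATT arms happen to contain different shares of aspirin-treated children, the ATT difference moves by the imbalance times the aspirin effect. The same holds in reverse for the aspirin comparison. The plan adjusts for four baseline factors but does not name the other factor of its own design.

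What is at stake is precision in a non-inferiority comparison, in a trial that closed recruitment at 369 rather than 400 (Study status).

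**Working it through.** **Inputs from the article (Sample size, Study status, Box 3).** Mortality 20% control and 17% intensified; margin 10 points; 90% power; two-sided 5% alpha; 5% loss; 369 enrolled; 1:1 allocation in both randomisations; starred factors with 3 × 2 × 2 × 2 = 24 cells (HIV status taken as two levels).

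**Assumed, because the article gives no figure.** The effect δ of aspirin on mortality: 5 and 8 points as working values. As an upper scenario, 13.4 points (mortality halved, 26.7% against 13.3%, averaging 20%) and 16 points (the planned effect on death or severe impairment, applied to death alone). The two allocations are taken as independent.

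**The plan's own figure.** "Based on a non-inferiority margin of 10%, 394 (rounded to 400) children would be needed to demonstrate non-inferiority". Per arm: (1.960 + 1.282)² × (0.20×0.80 + 0.17×0.83) / 0.13² = 187.2. Total 374.4; divided by 0.95, 394.1. The stated 394 reproduces.

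**Standard error as planned.** With 380 evaluable (190 per arm), SE = √[(0.1600 + 0.1411)/190] = 3.98 points. Power = Φ(13/3.98 − 1.96) = 90.4%.

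**Chance imbalance.** The aspirin share in an arm of N/2 children has variance 0.25/(N/2), so the between-arm difference has variance 1/N. At N = 400 its SD is 5.0 points. The SD of the shift in the ATT estimate is δ/√N.

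**Variance removed by adjustment.** (δ²/380)/SE². Adjusted power and required N follow by scaling SE² by one minus this share. The last column comes from a simulation (40,000 runs, 380 evaluable) comparing the crude difference with the difference stratified by aspirin; the minimisation factors were not simulated.

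| δ (points) | SD of shift, N = 400 | Variance removed | Power | Required N | Non-inferiority conclusions differ |
|---|---|---|---|---|---|
| 0 | 0 | 0 | 90.4% | 394 | 0.6% |
| 5 | 0.25 | 0.4% | 90.5% | 392 | 0.9% |
| 8 | 0.40 | 1.1% | 90.7% | 390 | 1.3% |
| 13.4 | 0.67 | 3.0% | 91.2% | 382 | not run |
| 16 | 0.80 | 4.3% | 91.6% | 377 | 3.0% |

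**Validity without the term.** Across the simulated settings the crude analysis had absolute bias of 0.00 to 0.04 points, coverage of 94.8% to 95.0% and non-inferiority type I error of 2.5% to 2.6%. With stratification by aspirin, type I error was about 2.6%.

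**Randomisation 2.** With 50% against 34% and 200 per arm, SE = √[(0.2500 + 0.2244)/200] = 4.87 points. An assumed ATT effect of 3 to 10 points on mRS 5–6 gives a shift SD of 0.15 to 0.5 points, or 3% to 10% of that SE.

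**Sparsity if aspirin is crossed into the strata.** At 369 children, 369/24 = 15.4 per cell becomes 369/48 = 7.7.

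**The case against.** The strongest reply is that nothing is wrong. A margin analysis adjusted for the minimisation factors, under a stated no-interaction assumption, is a recognised analysis, and the simulation confirms its error rates. This stands, and it limits the point to an improvement.

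A second reply is that the article is condensed. It does not say that the adjustment list is closed, it refers to a SAP that is not shown, and it does not describe the minimisation algorithm fully. This also stands. The SAP may already contain the term, and if the system balances one allocation over the other, the shifts are smaller than those tabulated.

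A third reply is that adding aspirin to the Cochran-Mantel-Haenszel strata would worsen the sparsity that the article already foresees. It stands against that particular remedy, not against a main-effects model.

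A reader might infer something stronger: that the protocol expects aspirin to halve mortality, so that chance imbalance threatens the non-inferiority conclusion. The documents do not support this. The 50% reduction cited under Sample size is the result of a small adult trial (n=118, low-dose aspirin), not a design assumption for mortality here. The article's background on aspirin reports no survival effect in the only paediatric trial (n=146), and the ethics section states equipoise.

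Nor should the shift be set against the room under the margin as if it were extra error. With about 351 analysed (369 × 0.95) and 20% mortality in both arms, SE is about 4.27 points and the observed difference must be below 10 − 1.96 × 4.27 = 1.6 points. The chance shift is already inside that SE. Even with mortality halved, a variance cut of about 3% moves the threshold only to about 1.75.

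**Conclusion.** The point holds as a minor improvement to a stated method. The text names the minimisation factors and not the other randomised treatment, so a known source of variation is left in both estimates. The loss is small: about 0.4% to 1.1% of the variance of the ATT difference for assumed aspirin effects of 5 to 8 points on mortality, 3% to 4% in the upper scenario, and none if aspirin does not affect mortality. Power changes by a few tenths of a point in the first range and by about one point in the second.

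These sizes rest on assumed aspirin effects, on independent allocations, and on a calculation that leaves out the minimisation factors. It would be wrong to conclude that either primary estimate is biased or that any trial conclusion is at risk.

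**What to change.** For randomisation 2, add ATT arm as a covariate in the logistic model. This is one extra term. A conditional odds ratio can shift slightly when a prognostic covariate enters, so the covariate list should be fixed in advance.

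For randomisation 1, estimate the risk difference by standardisation from a regression model with main effects for the minimisation factors and aspirin/placebo. Do not cross aspirin into the existing strata. The allowance for alternative methods when strata are sparse can accommodate this, but the chosen method should be named.

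The cost is a small change to the wording of the primary estimator, to be prespecified before unblinding. No extra data are needed. The adjusted ATT analysis needs the aspirin code, which the aspirin comparison requires anyway. If the SAP already includes both terms, no change is needed.
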